5.5 DESIGN

Open randomized crossover trial in patients with non-dialysis chronic renal failure study:

• The effect of treatment with either ACE-I or AIIA on parameters of arterial stiffness assessed by the applanationtonometry method.
• The effect of treatment with both ACE-I and AIIA on parameters of arterial stiffness assessed by the applanationtonometry method.

The patient population is divided into 2 groups: one group with prior treatment with either ACE-I or AIIA (group I) and another group without prior treatment with either ACE-I or AIIA (group II). The study medication is as follows: the ACE inhibitor Enalapril and angiotensin receptor antagonist Candesartan. The study extends over three periods of 8 weeks. Patients in group I are randomized to receive either Enalapril in both the first and second periods or Candesartan in both the first and second periods. Patients in group II is randomized to either treatment with Enalapril or candesartan in the first period with a shift to the opposite drug in the second period.
Common to both groups is a double treatment with both Enalaprilat and Candesartan in the third period.
There will be carried out measurements at baseline and after the first, second and third period. Each study includes measurement by the applanationtonometry method where the tonometry is placed with gentle pressure towards the skin above the radial artery , thereby providing data for pulse wave analysis. Subsequently, measurements are performed equivalent to the radial, carotid and femoral arteries, thereby providing data for pulse wave velocity determination. The study design is shown in flow diagrams attached as Annex Ia + b.
There must be delivered 24 h urine collection before baseline and after every period. Chromium-EDTA clearance is carried out before and at the last visit in the trial.

*Patients receiving ACE-I or AIIA therapy prior to the trial.*
Pulse wave measurements are carried out at baseline and after each treatment period of 8 weeks, a total of 4 times. In addition comes 6 clinical control sessions and two appearances for the making of Chromium-EDTA clearance before and after the project.

Measurement I (start)

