• At the first day of the study the patient meets fasting from midnight and without smoking, but with permission to drink water. Alcohol should not be taken for 24 hours before study start. The patient waits to take his medication until after the study. For patients with diabetes, however, a light breakfast is consumed at home and the usual medications for diabetes, all medicines taken after the study. Investigations commenced approx. at. 9:00 after blood sampling and then 15 min. rest in supine position. The studies are carried out in a quiet room with ambient temperature 20-22 degrees. A total of 2 measurements are carried out by the same investigator.
After the measurement the patient's habitual ACE-I or AIIA therapy is discontinued and patients are randomized to a scenario with either Enalapril in the first and second periods (ACE-I group) or treatment with Candesartan in the first and second period (AIIA group). Common to both randomization groups is a common dual blockade with both Enalapril and Candesartan in the third period.
The ACE-I group is started in tablet Enalapril 5 mg daily and is given tablets until the next appointment. AIIA group is started in tablet Candesartan 4 mg daily and are given tablets until next appointment. For women of childbearing age, the drugs will only be supplied in case of a negative pregnancy test.

The patient must before start of treatment have had a Chromium-EDTA clearance performed as well as a 24 h urine collection, which is attempted planned for the day of measurement I.

Adjustment of medicine and clinical control Ia (after 2-3 weeks)
• Attendance in the morning for blood pressure measurement and blood sampling. Control of treatment. The AIIA-group is increased to a tablet of candesartan 8 mg daily and the ACE-I group is increased to a tablet Enalapril10 mg daily. Both groups were handed out tablets for next appointment.

Adjustment of medicine and clinical control Ib (after 5-6 weeks weeks)
• Attendance in the morning for blood pressure measurement and blood sampling. Control of treatment. The AIIA group increased to a tablet of candesartan 16 mg daily and the ACE-I group increased to a tablet Enalapril 20 mg daily. Both groups were handed out tablets for next appointment.

Measurement II (after approx. 8 weeks, 1^st^ period)

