• The patient meets fasting from midnight and without prior smoking, but with permission to drink water. Alcohol should not be taken for 24 hours before study start. A 24 hour urine collection is delivered for analysis. The patient is taking the study medication approx. 2 hours before meeting time. Any other medication is to be taken after the measurements on that day. For patients with diabetes however, a light breakfast and the usual medications for diabetes and the study medication are consumed at home, all other medication is to be taken after the measurement that day. Investigations are started approx. at. 9:00 after blood sampling and then 15 min. rest in the supine position. The measurements are carried out in a quiet room with ambient temperature 20-22 degrees. A total of 2 measurements are performed by the same investigator.
After the measurement, the patients in the ACE-I group continue taking a tablet of Enalapril 20 mg daily and patients in the AIIA group continue taking tablet candesartan 16 mg daily. They are handed out tablets to the next appointment.

Adjustment of medicine and clinical control IIa (after 10-11 weeks)
• Attendance in the morning for blood pressure measurement and blood sampling. Control of treatment. Patients in the ACE-I group continue on tablet Enalapril 20 mg daily. The AIIA group continues on tablet candesartan 16 mg daily. They are handed out tablets to next appointment.

Adjustment and control IIb (after 13-14 weeks)
• Attendance in the morning for blood pressure measurement and blood sampling. Control of treatment. Patients in the ACE-I group continue on tablet Enalapril 20 mg daily. The AIIA group continues on tablet candesartan 16 mg daily. They are handed out tablets to next appointment.

Measurement III (after about 16 weeks, second period)

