5.12 PRACTICAL PERFORMANCE

Patients who are interested in participating in the study are informed about the project. The written patient information (Annex IA, IB and III) obtained and reviewed and a possibly. consent is issued.

A time schedule is agreed for Chromium-EDTA clearance, the measurements and the clinical controls.

Demographic data is recorded, possibly using the patient record.

*Randomization*Prior treatment with ACE-I/AIIA: Randomization is done by drawing lots from a bag in which there are 40 notes. Half of these are inflicted ACE-I treatment and the other half is applied AIIA therapy. Randomization for the group of patients without prior ACE-I/AIIA is done in the same way by lot from a bag, half of the 20 notes bearing the ACE-I in the first period and AIIA in the second period and the other half is applied AIIA in the first period, and ACE-I in the second period. The result of the randomization is recorded in the patient's Case Report Form.

*Measurement I-VI*The day before the measurements the patient collects urine in a dunk.
At the day of the first measurement the patient does not take his usual medications until after the measurement. In case of diabetes, the habitual diabetes medication is taken as usual, but all other medications are taken after the measurement. At the other measurements the study medication is taken 2 hours before meeting time, but all other medications taken after the measurement, except from antidiabetic medication. On arrival the patient is weighed. The patient brings 24 h urine collection.

At study start (baseline) blood sampling is taken in a peripheral vein for analysis of: b-hemoglobin, b-leukocytes, b-platelets, p-bilirubin, p-ALT, p-alkaline phosphatase, hsC-reactive protein, p-creatinine , p-urea, p-sodium, p-potassium, p-bicarbonate, glucose, p-albumin, p-cholesterol, p-triglyceride, p-urate, p-parathyroid hormone and p-homocysteine.

At the other measurements and clinical controls the following blood samples are taken for analysis: b-hemoglobin, p-creatinine, p-urea, p-albumin, p-potassium and p-sodium.

The patient is placed supine on a bed in a quiet room and is resting for 15 minutes. A blood pressure is recorded by a mercury sphygmomanometer.

Data is recorded in the schedules attached as Annex IIA and IIB.

*Clinical controls*

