5.14 STATISTICS

Primary endpoint is PWV (brachial) and PWV (aortic) with a minimum clinically relevant difference of 1 m/s. Based on previous reproducibility (29) the standard deviation is 1.1 and 0.75 m/s for brachial and aortic PWV, respectively. The power of the t-test by comparing the two distributions is at n = 20 at 0.82 and 0.99 for brachial and aortic PWV, respectively.

A P-value less than 0.05 is considered significant.
Data from discontinued subjects can be assessed for each completed treatment period. Withdrawn participants are replaced by new subjects, so the size of patient population is achieved.
A professional statistician is associated with the project and has advised in creating the design. Data processing will be conducted under the guidance of the very same professional statistician.

**6. Quality control and quality assurance**General procedures for quality control and quality assurance will be followed in accordance with the ICH GCP Guidelines. Data will be monitored by the University GCP unit. In connection with the informed consent a permission is obtained from the study participants, that the research ethics committee, the Medicines Agency and the GCP unit can access information about their health. A copy of the proposed text is attached as Annex IIIa.

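### In previously treated patients, baseline tonometry is done with that day's ACE-I/AIIA withheld, but every later measurement follows a dose about 2 hours before, so change from baseline includes a dose-timing difference

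*Protocol*

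**What the plan says.** Section 5.6 plans 60 patients: 20 on prior ACE-I, 20 on prior AIIA and 20 on neither. The first two sets form Group I (n = 40) and the third forms Group II.

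For Group I at Measurement I, section 5.5 says "The patient waits to take his medication until after the study". The habitual blocker is stopped only once that measurement is done: "After the measurement the patient's habitual ACE-I or AIIA therapy is discontinued". There is no washout, so the Group I baseline is an on-treatment state with that day's dose held back.

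For Measurements II, III and IV, section 5.5 says each time "The patient is taking the study medication approx. 2 hours before meeting time".

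Section 5.12 states the two rules together. For baseline: "At the day of the first measurement the patient does not take his usual medications until after the measurement". For the rest: "At the other measurements the study medication is taken 2 hours before meeting time". Apart from antidiabetic drugs, all other medication is taken after the measurement at every visit.

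The drug and dose also change after baseline. Group I moves from an unspecified habitual agent and dose to enalapril or candesartan, titrated to 20 mg or 16 mg.

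**The concern.** Sections 5.4 and 5.5 take care over measurement conditions: fasting, smoking, alcohol, time of day, supine rest, room temperature and the same investigator. The condition closest to the intervention, the interval since the last renin-angiotensin blocker, is left different between baseline and every later measurement in two thirds of the patients. The protocol neither gives a reason for this nor reconciles it.

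The first design objective in section 5.5 is the effect of either drug on arterial stiffness, and a baseline measurement is taken in both groups. A Group I change from baseline is therefore a natural thing to report. It would contain three components: timing of the dose, change of agent, and change of dose. If the habitual drug is taken in the morning (an assumption; the protocol does not give the time of intake), baseline is taken at the end of the dosing interval and the later values shortly after a dose. The mismatch then favours an apparent benefit.

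**Working it through.** **Dose timing by visit, from sections 5.5 and 5.12**

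| | Measurement I | Measurements II–IV |
|---|---|---|
| Group I, ACE-I/AIIA | on habitual drug, that day's medication withheld | study drug about 2 h before meeting time |
| Group II, ACE-I/AIIA | none | study drug about 2 h before meeting time |
| Both groups, other non-diabetic medication | after the measurement | after the measurement |

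For Group II the baseline rule is harmless, because there is no ACE-I/AIIA to withhold. In Group I every patient follows the withholding rule at I and the post-dose rule at II–IV. Timing is therefore completely confounded with baseline versus follow-up, and adjustment cannot recover it.

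**Which contrasts are touched**

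- Measurement IV against II or III (dual versus single): same timing at each, not affected.
- Enalapril against candesartan within Group I: both randomised arms share the baseline rule, so the shift largely cancels unless it differs by drug.
- Group I change from Measurement I: affected.

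**The plan's own figure.** Section 5.14 says "the standard deviation is 1.1 and 0.75 m/s for brachial and aortic PWV, respectively" and gives power 0.82 and 0.99 at n = 20 for 1 m/s. Taking 20 per arm, two-sided 0.05 and a normal approximation:

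- Brachial: SE = 1.1 × √(2/20) = 0.348; 1/0.348 = 2.875; Φ(2.875 − 1.96) = 0.82.
- Aortic: SE = 0.75 × √(2/20) = 0.237; 1/0.237 = 4.216; Φ(4.216 − 1.96) = 0.99.

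The noncentral t gives 0.80 and 0.98. A paired test at n = 20 with 1.1 as the SD of differences gives 0.97. The stated SDs thus act as per-group SDs, and this check does not dispute the stated power.

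**How much a timing shift could matter.** Inputs: n = 40 (section 5.6), SDs 1.1 and 0.75 and alpha 0.05 (section 5.14), two-sided (assumed). The documents give no timing effect, so shifts of 0.1, 0.3 and 0.5 m/s are assumed. The SD of within-patient differences is not given either, so two readings bracket it: the stated SD, and √2 times the stated SD (independent measurements: 1.1 × 1.414 = 1.56; 0.75 × 1.414 = 1.06).

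With no true drug or dose effect, the noncentrality is shift × √40 / SD of differences, with 39 degrees of freedom and critical value 2.023. For example, brachial with SD 1.1 and shift 0.3 gives 0.3 × 6.325 / 1.1 = 1.725, and a rejection probability of 0.39.

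| SD of differences | 0.1 m/s | 0.3 m/s | 0.5 m/s | 95% CI half-width (2.023 × SD/√40) |
|---|---|---|---|---|
| Brachial 1.56 | 0.07 | 0.22 | 0.51 | 0.50 |
| Brachial 1.1 | 0.09 | 0.39 | 0.80 | 0.35 |
| Aortic 1.06 | 0.09 | 0.42 | 0.83 | 0.34 |
| Aortic 0.75 | 0.13 | 0.69 | 0.98 | 0.24 |

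The nominal rate is 0.05. Assumed shifts of 0.3 to 0.5 m/s are of the same order as the half-widths.

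**The case against.** The strongest reply is that no comparison the protocol states for testing is biased. The hypothesis in section 5.1 is dual versus single blockade, with ACE-I versus AIIA alongside, and section 5.14 names no change-from-baseline test and no analysis at n = 40. This stands, and it limits how serious the point is.

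Second, the Group I change is hard to interpret anyway: it is uncontrolled, starts on treatment and mixes switching with titration. This also stands. Matching the timing does not turn it into single blockade versus none; only Group II can supply that. It is still worth removing the one confounder that the visit instruction itself creates.

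Third, the size is assumed throughout, and rejection probabilities from 0.07 to 0.98 establish no magnitude. That is correct. The table shows what follows if a shift exists, not that one does.

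Fourth, the direction depends on morning intake. For evening takers no dose is skipped, although the interval since the last dose still differs from later visits.

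Fifth, one baseline rule for both groups is simple, and taking the intervention before later measurements is deliberate. That explains each rule on its own but not the mismatch within Group I. Nor can the documents show that 2 hours is equivalent across the habitual agents in use, so matching the interval reduces the difference without guaranteeing its removal.

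**Conclusion.** The concern holds. In Group I, change from Measurement I contains a systematic dose-timing difference that cannot be separated from the effect of changing drug and dose. Its size is unknown. On assumed shifts of 0.3 and 0.5 m/s, timing alone would give a significant paired result at n = 40 with probability 0.22–0.39 and 0.51–0.80 (brachial), or 0.42–0.69 and 0.83–0.98 (aortic). At 0.1 m/s it would matter little. These figures rest on the assumed shifts, the two readings of the SD of differences, and a paired test that the protocol does not specify. The main hypothesis and the power basis are untouched. This is a change that should be made because it is cheap and cannot be made good at analysis; it does not invalidate the trial.

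**What to change.** In section 5.5 (Measurement I, patients with prior ACE-I/AIIA) and in section 5.12, change the baseline instruction for Group I so that the interval from the last ACE-I/AIIA dose to tonometry matches Measurements II–IV. Suggested wording: *On the day of Measurement I, patients with prior ACE-I/AIIA take that drug about 2 hours before they are due to attend; all other medication except antidiabetic drugs waits until the measurement is finished.* Water is already allowed while fasting, so the visit need not change.

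Record the time of the last ACE-I/AIIA dose in the Case Report Form at all four measurements. When reporting, do not present Group I change from baseline as the effect of single blockade against none.

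The cost is one sentence in each of the two sections and one Case Report Form field. The drawback is that patients who usually take the drug in the evening must move that dose to the morning for Measurement I, and the two groups will have different baseline instructions.

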• The patient meets fasting from midnight and without prior smoking, but with permission to drink water. Alcohol should not be taken for 24 hours before study start. A 24 hour urine collection is delivered for analysis. The patient is taking the study medication approx. 2 hours before meeting time. Any other medication is to be taken after the measurements on that day. For patients with diabetes however, a light breakfast and the usual medications for diabetes and the study medication are consumed at home, all other medications is to be taken after the measurement that day. Investigations are started approx. at. 9:00 after blood sampling and then 15 min. rest in the supine position. The measurements are carried out in a quiet room with ambient temperature 20-22 degrees. A total of 2 measurements are performed by the same investigator.
After the measurement, the patients in the ACE-I group are supplemented with tablet candesartan 4 mg daily. Tablet Enalapril is continued in the same dose of 20 mg daily. Patients in the AIIA group is supplemented with Enalapril tablet 5 mg tablet daily and Candesartan is continued in the same dose of 16 mg daily. For both groups tablets are handed out to the next appointment.

Adjustment of medicine and clinical control IIIa (after 18-19 weeks)
• Attendance in the morning for blood pressure measurement and blood sampling. Control of treatment.
In the ACE-I group the dose of tablet candesartan is increased to 8 mg daily. Enalapril continues in the same dose of 20 mg daily. The AIIA group is increased to a tablet Enalapril 10 mg tablet daily and Candesartan continues in the same dose of 16 mg daily. They are handed out tablets to the next appointment.

Adjustment of medicine and clinical control IIIa (after 21-22 weeks)
• Attendance in the morning for blood pressure measurement and blood sampling. Control of treatment.
In the ACE-I group the dose of a tablet candesartan is increased to 16 mg daily. Enalapril continues in the same dose of 20 mg daily. The AIIA group is increased to a tablet Enalapril 20 mg tablet daily and Candesartan continues in the same dose of 16 mg daily. They are handed out tablets to the next appointment.

Measurement IV (after approx. 24 weeks, third period)

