Group A is started treatment with tablet Enalapril 5 mg daily. Group B is started treatment with tablet candesartan 4 mg daily. They are handed out tablets to next appointment. For women of childbearing age, the drugs will only be supplied in case of a negative pregnancy test.

The patient must before start of treatment have had a Chromium-EDTA clearance performed as well as a 24 h urine collection, which is attempted planned for the day of measurement I.

Adjustment of medicine and clinical control Ia (after 2-3 weeks)
• Attendance in the morning for blood pressure measurement and blood sampling. Control of treatment. Patients in group A is increased to tablet Enalapril 10 mg daily and patients in group B increased to tablet candesartan 8 mg daily. Both groups are handed out tablets for the next appointment.

Adjustment of medicine and clinical control Ib (after 5-6 weeks)
• Attendance in the morning for blood pressure measurement and blood sampling. Control of treatment. Patients in group A are increased to tablet Enalapril 20 mg daily and patients in group B are increased to tablet candesartan 16 mg daily. Both groups are handed out tablets for the next appointment.

Measurement II (after approx. 8 weeks 1^st^ period)
• The patient meets fasting from midnight and without prior smoking, but with permission to drink water. Alcohol should not be taken for 24 hours before study start. A 24 hour urine collection is delivered for analysis. The patient is taking the study medication approx. 2 hours before meeting time. Any other medication is to be taken after the measurements on that day. For patients with diabetes however, a light breakfast and the usual medications for diabetes and the study medication are consumed at home, all other medications is to be taken after the measurement that day. Investigations are started approx. at. 9:00 after blood sampling and then 15 min. rest in the supine position. The measurements are carried out in a quiet room with ambient temperature 20-22 degrees. A total of 2 measurements are performed by the same investigator.
After the measurement the patients in group A are changed to tablet Candesartan 4 mg and will no longer take Enalapril tablet. Patients in group B are changed to tablet Enalapril 5 mg daily and will no longer take tablet Candesartan. They are handed out tablets to the next appointment.

Adjustment of medicine and clinical control IIa (after 10-11 weeks)

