• Attendance in the morning for blood pressure measurement and blood sampling. Control of treatment. Patients in group A are increased to tablet candesartan 8 mg daily. Patients in group B are increased to tablet Enalapril 10 mg daily. They are handed out tablets to the next appointment.

Adjustment of medicine and clinical control IIb (after 13-14 weeks)
• Attendance in the morning for blood pressure measurement and blood sampling. Control of treatment. Patients in group A are increased to tablet candesartan 16 mg daily. Patients in group B are increased to tablet Enalapril 20 mg daily. They are handed out tablets to the next appointment.

Measurement III (after about 16 weeks, second period)
• The patient meets fasting from midnight and without prior smoking, but with permission to drink water. Alcohol should not be taken for 24 hours before study start. A 24 hour urine collection is delivered for analysis. The patient is taking the study medication approx. 2 hours before meeting time. Any other medication is to be taken after the measurements on that day. For patients with diabetes however, a light breakfast and the usual medications for diabetes and the study medication are consumed at home, all other medications is to be taken after the measurement that day. Investigations are started approx. at. 9:00 after blood sampling and then 15 min. rest in the supine position. The measurements are carried out in a quiet room with ambient temperature 20-22 degrees. A total of 2 measurements are performed by the same investigator.
After the measurement the patients in group A are supplemented with tablet Enalapril 5 mg daily in addition to tablet candesartan 16 mg daily. Patients in group B are supplemented with tablet candesartan 4 mg daily in addition to tablet Enalapril 20 mg daily. They are handed out tablets to the next appointment.

Adjustment of medicine and clinical control IIIa (after 18-19 weeks)
• Attendance in the morning for blood pressure measurement and blood sampling. Control of treatment.
Patients in group A are increased to tablet Enalapril 10 mg daily and continued on the same dose of tablet Candesartan. Patients in group B are increased to tablet candesartan 8 mg daily and continued on the same dose of Enalapril tablets. They are handed out tablets to the next appointment.

Adjustment of medicine and clinical control IIIa (after 21-22 weeks)
• Attendance in the morning for blood pressure measurement and blood sampling. Control of treatment.

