Patients in group A are increased to tablet Enalapril 20 mg daily and continued on the same dose of tablet Candesartan. Patients in group B are increased to tablet candesartan 16 mg daily and continued on the same dose of Enalapril tablets. They are handed out tablets to the next appointment.

Measurement IV (after approx. 24 weeks, third period)
• The patient meets fasting from midnight and without prior smoking, but with permission to drink water. Alcohol should not be taken for 24 hours before study start. A 24 hour urine collection is delivered for analysis. The patient is taking the study medication approx. 2 hours before meeting time. Any other medication is to be taken after the measurements on that day. For patients with diabetes however, a light breakfast and the usual medications for diabetes and the study medication are consumed at home, all other medications is to be taken after the measurement that day. Investigations are started approx. at. 9:00 after blood sampling and then 15 min. rest in the supine position. The measurements are carried out in a quiet room with ambient temperature 20-22 degrees. A total of 2 measurements are performed by the same investigator.
After the measurement, the study medication is discontinued and the patient returns to his habitual medication. Eventually the patient is having a Chromium-EDTA clearance performed.

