5.7 INCLUSION CRITERIA

The patient can be included in the project if the answer is YES to the following:
- Age between 18 and 75 years
- Have submitted voluntary written informed consent
- Have plasma creatinine between 150-350 µmol/l
- Systolic blood pressure> 110 mmHg
- Negative pregnancy test in fertile women

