5.8 EXCLUSION CRITERIA

The patient may not be included in the project if the answer is YES to at least one of the following:
- Treatment with both ACE-I and A-II-A at inclusion time
- Pregnancy or lactation
- Treatment with immunosuppressive, steroids or NSAIDs
- Severe chronic heart failure (NYHA III-IV)
- Chronic liver disease
- Suspected or confirmed renal artery stenosis
- Cardiac arrhythmia and / or implantable pacemaker
- AMI or cerebrovascular event within the last 3 months
- Allergy to ACE-I or AIIA
- Amputation of a limb or crural or femural amputation.
- Dementia or a mental condition that prevents understanding of study requirements
- Dialysis or transplantation
- Treatment with aldosterone antagonists
- Plasma-potassium> 5.5 mmol/l
- Other severe chronic non-renal disease

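### Section 5.5 fixes every dose increase, and the start of the second blocker, with no potassium or blood pressure condition; on treatment there is no step between escalation and withdrawal

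*Protocol*

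**What the plan says.** **Dose steps (Protocol 5.5).** Patients with prior ACE-I/AIIA therapy start at the lowest dose. At control Ia, weeks 2-3, "The AIIA-group is increased to a tablet of candesartan 8 mg daily and the ACE-I group is increased to a tablet Enalapril10 mg daily"; full dose follows at weeks 5-6. At Measurement III, about week 16, the AIIA group is "supplemented with Enalapril tablet 5 mg tablet daily and Candesartan is continued in the same dose of 16 mg daily", and the ACE-I group gets candesartan 4 mg on top of enalapril 20 mg. At weeks 18-19, "In the ACE-I group the dose of tablet candesartan is increased to 8 mg daily", with the last increase at weeks 21-22.

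Patients without prior therapy follow the same form: "Patients in group A is increased to tablet Enalapril 10 mg daily and patients in group B increased to tablet candesartan 8 mg daily" at control Ia, then "After the measurement the patients in group A are supplemented with tablet Enalapril 5 mg daily in addition to tablet candesartan 16 mg daily" at Measurement III, and at weeks 21-22 "Patients in group A are increased to tablet Enalapril 20 mg daily and continued on the same dose of tablet Candesartan".

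**Numeric limits.** Section 5.7 requires "Systolic blood pressure> 110 mmHg". Section 5.8 excludes "Plasma-potassium> 5.5 mmol/l". Both govern entry.

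**On treatment.** Section 5.9 withdraws patients for intractable hyperkalemia and for unacceptable side effects, neither with a value, and for a creatinine rise of more than 30% from baseline. Section 7.2 repeats withdrawal for adverse effects that cannot be tolerated. Section 5.12 says in general terms that the medication is adjusted at the clinical controls, and 5.13 says titration follows standard practice.

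**The concern.** Section 7.2 lists hyperkalemia and hypotension as adverse effects of both drugs, and 5.7 enrols patients with plasma creatinine of 150-350 µmol/l. Potassium and blood pressure are taken at every control visit, yet no result is tied to what happens to the dose at that visit. Monitoring protects a patient only if an abnormal value changes an action.

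Two things are at stake. The first is safety: read literally, 5.5 adds or raises a second blocker whatever the visit's potassium or pressure. The second is conduct: where an investigator departs from the schedule on clinical grounds, nothing makes that decision alike across patients. The trial is open and the investigator packs the medicine, so unwritten dose deviations bear on the dual-versus-single comparison that 5.1 states as the hypothesis.

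**Working it through.** The plan gives no figure on this point to reproduce. The check compares the rules at entry with the rules on treatment, counts the steps, and works out the time to the next sample.

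**1. Limits at entry and on treatment**

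| Variable | Numeric limit at entry | Numeric limit on treatment | Other on-treatment cover |
|---|---|---|---|
| Potassium | 5.5 mmol/l (5.8) | none | withdrawal if intractable (5.9), or as an unacceptable or intolerable side effect (5.9, 7.2) |
| Systolic pressure | 110 mmHg (5.7) | none | withdrawal as an unacceptable or intolerable side effect (5.9, 7.2) |
| Creatinine | 150-350 µmol/l (5.7) | rise >30% from baseline (5.9) | not needed here |

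Creatinine is not part of this point, because it has a numeric on-treatment rule.

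**2. Unconditioned steps (5.5)**

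- Prior therapy: 2 increases in period 1 + 0 in period 2 + 1 second-drug start + 2 increases in period 3 = 5.
- No prior therapy: 2 + 2 + 1 + 2 = 7, not counting the switch of drug at week 8.
- Both strata: 1 start + 2 increases = 3 steps into or within dual therapy.

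None of these steps carries a potassium or blood pressure condition.

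**3. Time to the next scheduled blood sample after each dual-therapy step**

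Shortest interval = earliest next visit minus latest current visit; longest = latest next visit minus earliest current visit.

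- Start at about week 16, next visit weeks 18-19: 18 − 16 = 2 to 19 − 16 = 3 weeks.
- Increase at weeks 18-19, next visit weeks 21-22: 21 − 19 = 2 to 22 − 18 = 4 weeks.
- Increase at weeks 21-22, next visit about week 24: 24 − 22 = 2 to 24 − 21 = 3 weeks.

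The range is therefore 2 to 4 weeks by the stated windows. Section 5.12 gives every second to third week as the nominal interval.

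**4. A worked case**

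Take, as an illustration, a patient at weeks 18-19 without symptoms, with potassium 5.8 mmol/l and a creatinine rise below 30%. Since 5.8 > 5.5, this value would have barred entry. The creatinine rule does not apply. One high value is not shown to be intractable, and without symptoms it need not count as an unacceptable side effect. The dose line in 5.5 then raises the second drug while the first stays at full dose, and no repeat test is written.

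**The case against.** The strongest reply is that 5.5 is a target schedule. Each increase stands under a heading that speaks of adjusting medicine and follows blood pressure measurement and blood sampling. Section 5.12 mentions adjustment, and 5.13 refers to standard practice with approved drugs. Calling intractable hyperkalemia a reason for withdrawal implies some management first. The design also limits risk. Section 5.8 excludes aldosterone antagonists, NSAIDs, renal artery stenosis and severe heart failure. Forty of the 60 planned patients enter already on one blocker (5.6). By the dual step that stratum has been scheduled on full-dose single therapy for 16 − 6 = 10 to 16 − 5 = 11 weeks. The second drug starts at its lowest dose.

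Much of this stands, and it rules out stronger readings that a reader might infer:

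- *That hyperkalemia has a single on-treatment criterion.* It does not. The routes for unacceptable and intolerable side effects also cover it, and the plain-language description near the front of the protocol names raised potassium among the side effects.
- *That the judgement wording contradicts 5.5.* A target schedule with clinical adjustment is not a contradiction.
- *That 7.3 relies on frequent controls alone.* It also names patient selection by the entry criteria and 24-hour access to a nephrology doctor.

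The reply does not supply the missing step. The judgement wording permits a departure from the schedule but gives no threshold, hold, lower dose or retest. The withdrawal routes act only by removing the patient. The protocol does write conditions elsewhere: study drug is dispensed to women of childbearing age only after a negative pregnancy test, and creatinine has its 30% rule. A dose condition is thus within its scope, and is not something a statistical analysis plan would provide.

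**Conclusion.** The point holds and should be fixed. As written, every increase, and the start of the second blocker, goes ahead regardless of that visit's potassium or blood pressure, and nothing is described between full escalation and withdrawal. The size that can be stated is that of the rule: one numeric limit each for potassium and systolic pressure at entry, none on treatment, three unconditioned dual-therapy steps per patient, and 2 to 4 weeks to the next scheduled sample after each.

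The size of the harm is unknown. The documents give no on-treatment rate of potassium above 5.5 mmol/l or of hypotension, so no number of patients can be offered, and a claim that a given share would be harmed has no support. The conclusion also rests on the protocol text at hand. The Annex I flowcharts and the registration forms were not available, and a condition written there would change it. Confidence is medium, because clinical judgement would probably stop some of these steps in practice.

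**What to change.** In 5.5, make the second-drug start and each increase conditional on that visit's results, read before the new dose is taken:

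- If potassium is above 5.5 mmol/l, or there is symptomatic hypotension, or systolic pressure is below a floor that the sponsor sets, do not start or increase. Hold, or step down the drug most recently added or increased, and repeat the test before proceeding.
- Otherwise proceed as scheduled.

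Let the standard-practice wording in 5.13 refer to this rule. Leave the withdrawal criteria in 5.9 unchanged, including the >30% creatinine rule. Do not redefine intractable hyperkalemia as any value still above 5.5 mmol/l: that would force withdrawal just over the limit and, since 5.14 replaces withdrawn patients, could tilt the sample towards those who tolerate treatment. Using 5.5 mmol/l as a hold limit borrows the protocol's entry value; the sponsor may justify another.

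Record the dose actually taken at Measurements II, III and IV. The medication accounts in 5.13 already supply most of this.

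**Cost.** A short amendment and no new scheduled tests, since potassium and blood pressure are already taken at these visits. The protocol does not say that control-visit results are back before tablets are handed out, so a same-day or telephoned result may be needed, plus a repeat potassium for held patients. Some patients will be measured below full dose. That must be reported and may slightly dilute the dual-versus-single contrast.
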